## Abstract

Ventilator-associated pneumonia is one of the most severe complications of critically ill patients that need mechanical respiratory support, as it poses a significant risk of prolonging hospitalization, disability, and even death. This is why physicians worldwide target newer methods for prevention, early diagnosis, and early target treatment for this condition. There are few methods for a quick etiological diagnosis of pneumonia, especially point of care, and most are only readily available in some intensive care units. This is why a new, simple, and cheap method is needed for determining the bacteria that might be infectious in a particular patient. The manner in question is sonication. Method: In this prospective, observational, single-center study, endotracheal cannula specimens will be collected from at least 100 patients in our intensive care unit. This specimen will be submitted to a specific sonication protocol for bacteria to dislodge the biofilm inside the cannula. The resulting liquid will be seeded on growth media, and then a comparison will be made between the germs in the biofilm and the ones in the tracheal secretion of the patient. The primary purpose is to determine the bacteria before the appearance of a manifest infection.

## 1. Introduction

The most prevalent infection in the intensive care unit (ICU) is the hospital–acquired pneumonia (HAP) [1,2]. This group of conditions encompasses two different entities: ventilator-associated pneumonia (VAP) and high-severity pneumonia developed during hospitalization. VAP is a type of pneumonia that develops in mechanically ventilated patients. The reported incidence of VAP is extensive, ranging from 1.9–3.8 per 1000 days of mechanical ventilation in the USA to more than 18 per 1000 days in Europe [1]. The incidence of this type of pneumonia in Romania is probably even higher, but retrospective or prospective multicentric studies have not quantified its prevalence [2].

VAP occurs after 48 h of mechanical ventilation. The onset relative to hospital admission discriminates early pneumonia (under five days) from late pneumonia (over five days) [3,4].

VAP diagnosis is made on clinical, paraclinical, and radiological criteria. For the radiological criterion to be met, two successive chest radiographs showing new or progressive lung infiltrates or a single chest radiograph without a medical history of underlying heart or lung disease are required. It should be accompanied by at least one of the following: new onset fever (without any other cause) or changes in the leukocytes number (≤4000 mm^3^ or ≥12,000 mm^3^) and at least two of the following signs: purulent sputum, (cough, dyspnoea—for HAP), declining oxygenation, increased oxygen requirements(4).

The most common causes of VAP are bacteria, but viruses are increasingly recognized. Fungal pathogens are uncommon except for immunocompromised patients [5] and patients treated with wide-spectrum or long-term antibiotic treatments. The frequency of different pathogens can vary according to geographic region and according to hospital and hospital clinical activity. The bacteria most frequently isolated from patients with VAP are aerobic gram-negative bacteria (Klebsiella pneumoniae, Acinetobacter species, Pseudomonas aeruginosa, Enterobacter spp, Stenotrophomonas maltophilia, Serratia marcescens) in more than 60% of the cases [6,7,8] and gram-positive cocci (Staphylococcus aureus, particularly MRSA). The rates of polymicrobial infections vary even more and are usually associated with aspiration, and the incidence is higher in adults with acute respiratory distress syndrome (ARDS) [9]. The viral etiology of hospital-acquired pneumonia appears most commonly seasonal, including influenza, parainfluenza, adenovirus, and respiratory syncytial virus [9]. SARS-CoV has become one of the most prevalent viruses to be isolated in hospitalized patients in the last four years.

The complications associated with ventilation-associated pneumonia are multiple. Prolonged antibiotic therapy and mechanical ventilation increase the risk of serial colonization and reinfection with pathogens: recurrent pneumonia or Clostridium difficile colitis [5]. A possible risk is a cardiac decompensation triggered by the combination of hypoxemia and increased metabolic demands due to infection. It can manifest by acute ischemia, exacerbation of heart failure, and new onset arrhythmias [10].

A pooled analysis of randomized studies shows that attributable mortality from ventilator-associated pneumonia is estimated at 10% [10]. About one-third of HAP develops in ICU, with VAP accounting for 90% of cases. VAP occurs in 9–40% of intubated patients, representing the most frequent ICU-acquired infection [11]. The 28-day mortality rate for hospital-acquired pneumonia is around 30% among patients admitted to the ICU [12].

Along with the increased morbidity and mortality associated with VAP, this kind of healthcare-associated infection is of concern as it poses a substantial economic burden. The Society of Healthcare Epidemiology of America (SHEA) conducted a matched cohort study of the Premier database. It evaluated the impact of VAP on the length of stay (LOS) in the hospital and ICU, duration of mechanical ventilation, and hospital costs. Regarding expenses, SHEA demonstrated an increase in hospitalization costs by almost 40% [13].

Currently, few measures try to prevent ventilator-associated pneumonia, and even fewer cheap and accessible means of early diagnosis of this condition. Early diagnosis is essential as it prompts targeted antibiotic therapy and a faster resolution of pneumonia. The microbiologic tests (phenotypic, molecular, and rapid tests) have a series of advantages as an etiological diagnostic method for infection. Phenotypic tests are time-consuming, have limited ability to differentiate closely related species, and may not detect non-viable or slowly growing bacteria. With high sensitivity and specificity, molecular tests necessitate specialized equipment and expertise. Rapid tests, on the other hand, though quick and reliable, may have a lower sensitivity compared to molecular tests and may sometimes need validation or confirmation using other methods. The main disadvantage of the previously described methods is the lack of availability and the increased costs.

The purpose of using sonication as a detection method is to develop a cheap, sensitive, and specific method for microorganism detection from medical biofilms, including the ones formed on the intubation cannulas.

As there are many bio-film-related infections, from catheter-associated urinary tract infections to central line-associated bloodstream infections [14,15,16], one can only imagine that the intubation cannula can provide a perfect surface for bacteria to adhere to.

Sonication applies sound energy to agitate particles or discontinuous fibers in a solution or dislodge cells from certain surfaces [17]. The acoustic energy or the sound wave involves the conversion of an electrical signal into a physical vibration with a specific frequency and amplitude directed toward a substance [18,19].

Sonication was used mainly in domains only tangent to the medical field: pharmaceutical and cosmetics, and other industries, such as food, water, pesticides, ink, paint, coating, nanocomposite, metalworking, wood product, wood treatment, and many others. It is helpful with the production of nanoparticles such as nanoemulsions [20], nanocrystals, liposomes, and wax emulsions, as well as for water purification, degassing, extraction of seaweed polysaccharides [17] and plant oil, extraction of anthocyanins and antioxidants [21], production of biofuels, crude oil desulphurization, cell disruption, polymer and epoxy processing, adhesive thinning, and a lot of other processes.

In the last decade, sonication has become more and more influential in the biomedical field as the method used to determine the bacteria associated with different kinds of biofilms.

To use sonication for microorganism dislodgement from different surfaces, a low sonication condition is needed to obtain viable bacteria. It represents a low-intensity technique, which is not destructive and consists of a series of sound waves with certain amplitude, frequency, distance, time, and temperature [17,22].

The immediate effect of sound is the modification of the permeability of the cellular plasma membrane by applying the acoustic cavitation of microbubbles to enhance delivery. This specific phenomenon is called sonoporation [23]. Depending on the expected result, sonoporation can have beneficial or undesirable effects. Due to the possibility of the appearance of cavitation in aqueous solutions, the cell wall of the microorganisms is at risk of destruction [17,22,23]. Due to the collapse of the bubbles, a high shear force is generated in the environment that breaks the cell wall and membranes [24]. Thus, if the purpose of sonication is to dislodge the bacteria from the surfaces and to keep them viable, the variables of the sound waves must be adjusted so that the plasmatic cell membrane remains intact. The ultrasound waves can then have two types of effects based on the result on the microorganism: reversible (or repairable), when the pores induced in the cell membrane can reseal, leading to cell survival, and irreversible (or lethal), when the cell dies because of the cellular lysis [23,25].

Studies performed in vitro demonstrated that different bacterial species have additional resistance to sound waves. If the sonication protocol is also associated with increases in the temperature of the environment, the destruction of the bacteria is obtained. Gram-positive bacteria were generally more resistant to the effect of ultrasounds than gram-negative ones [26,27]. The layer of proteoglycans in the gram-positive cellular wall is usually much thicker than that in the gram-negative microorganisms. Lipopolysaccharides are the factors that significantly contribute to the structural integrity and protect the membrane of the latter category. In this case, the set target for the sound waves should be the inner layer of the membrane, the one consisting of lipopolysaccharides [28]. On the other hand, spores, for instance, are very resistant to sonication. There has been a report by Pitt and Ross [29] affirming that the cell wall of the spore can even grow under the influence of low sonication (≤2 W/cm^2^). It is the consequence of pore formation in the cell wall, which facilitates the transport of nutrients and small particles (water, carbon dioxide, peptides, and amino acids) in the solution, and of the inability of ultrasound to remove cells from the surfaces altogether.

It is well known that many different microorganisms can adhere to surfaces and form biofilms, but the adherence strength is different. Sonication can dislodge any biofilm, but not all bacteria can be easily cultivated on media because some necessitate special growth media and environments, and others are killed before inoculation. This being said the precipitation of the sonication fluid is more likely to contain gram-positive bacteria, mainly cocci and gram-negative ones. Particular types of microorganisms, such as mycobacteria or anaerobes, will not be isolated.

## 2. Methods

The present study is a prospective, observational, single-center study. It aims to isolate the bacteria in the biofilms of the tracheal cannulas of mechanically ventilated patients. The purpose of bacterial isolation is not only to compare with the bacterial load from tracheobronchial secretion but also to determine the optimal replacement time of the endotracheal cannulas in patients with prolonged mechanical ventilation.

It is estimated that more than 100 mechanically ventilated patients will be enrolled in the study over 12 to 18 months. The study will be located in the intensive care unit of Sibiu County Clinical Emergency Hospital, Romania. This ICU is a level I intensive care as it can assist a large variety of pathology: medical and surgical (general, thoracic and vascular surgery, neurosurgery, ENT, urology, trauma, and burns). It is organized on two floors with 12 single-bed rooms on each floor and four double-bed rooms for post-anesthesia care/intermediary care. 

This study will not affect the patient’s treatment plan and will be performed according to the attending physician’s indications. The endotracheal cannulas will be replaced if the patient’s clinical assessment allows this maneuver without endangering the well-being of the ill.

### 2.1. Aims of the Study

Detection of the bacteria in the biofilm formed inside the endotracheal cannulae.

Detection of the mean period during which the biofilm organizes in the lumen of the cannulae.

Determination of the optimal time to replace the intubation cannulae in patients that need mechanical ventilation for more than 48 h so that the contamination of the lower respiratory airways by dislodging the biofilm following suction maneuvres is prevented. 

Comparison of the microorganisms from the patient’s respiratory secretions with the bacterial load in the biofilm to initiate an early targeted antibiotherapy. Furthermore, it should be determined whether a clean cannula with a sterile biofilm can prevent the onset of VAP. 

Development of new methods to prevent VAP.

Final aim: decreasing the morbidity and mortality of critically ill patients by preventing or early and targeted treating VAP, reducing the LOS in the ICU and in the hospital with a secondary lowering of costs associated with hospitalization.

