### 2.3. Inclusion Criteria

Age between 18 and 100 years old.

Romanian citizenship.

Patients or legal representatives are informed and consent in writing to be part of the study.

Patients that require more than 48 h of mechanical respiratory support.

Exclusion criteria:

Under-aged patients.

Patients who do not consent or the consent could not be obtained.

The non-compliant collection of biological samples in patients.

Clinically unstable patients, so the samples could not be collected.

Less than 48 h of mechanical ventilation.

Non-Romanian nationality.

Eligible patients for the proposed research topic will be divided into two groups according to the cause of respiratory failure:

Group 1—respiratory failure due to pulmonary infection—confirmed bacterial pneumonia, bacterial bronchopneumonia, or with a high degree of clinical and biological suspicion (purulent tracheal secretions, paraclinical or imaging investigations highly suggestive of respiratory infection).

Group 2—respiratory failure secondary to non-infectious pulmonary conditions (severe asthma attack, pulmonary fibrosis) or extrapulmonary causes that need mechanical ventilation (polytrauma secondary to traffic accidents, falls, neurological or neurosurgical patients, patients with deteriorated consciousness that need airway protection).

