### 2.5. Microbiological Specimens—The Timing of the Sampling, Specimen Manipulation, Sonication Protocol

T_0_: tracheal aspirate collection in the first 2 h after the patient’s admission to the intensive care unit or after tracheal intubation and initiation of the invasive respiratory support.

Collection of a second tracheal aspirate 48–72 h after T_0_.

Replacement of the endotracheal cannula at 48–72 h from T_0_ and collection of a cannula specimen. The specimen will be sonicated according to an established protocol for bacterial sonication, and the sonication fluid will be inoculated onto bacterial culture media.

Collection of a third tracheal aspirate at 168–192 h from T_0_ if the patient requires prolonged mechanical ventilation or required reintubation less than 24 h from the time of extubation.

Change of the endotracheal cannula at 168–192 h from T_0_ and the collection of the cannula specimen, sonication, and fluid seeding onto growth media.

Sonication protocol: Orotracheal intubation cannula specimens will be sonicated for 30 min using an ultrasonic bath (BactoSonic14.2, Bandelin GmbH, Berlin, Germany) at a frequency of 42 kHz with a power of 0.22 W/cm^2^. The resulting sonication liquid is then homogenized, and 5–10 mL is centrifuged for 5 min at 2500 rpm. The resulting precipitate will be inoculated onto culture media and incubated at 37 degrees to inspect them for bacterial growth.

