Another area for improvement regarding this study is the impossibility of isolating certain species of bacteria. Bacteria that require special growth media can be included in this category: atypical bacteria, mycobacteria, and anaerobic bacteria. It has already been described in the medical literature that mycobacteria have the ability to adhere to surfaces and form biofilms [32]. The ultrastructure of the mycobacterial biofilms has been studied through different kinds of methods: Confocal laser scanning microscopy (CLSM) combined with fluorescent dyes, Nile Red, or LIVE/DEAD BacLight. This type of coloration is used to differentiate between the mycobacterial species by analyzing the phenotypic characteristic of biofilms (growth rate, live and dead bacteria, autofluorescence) [33]. Most anaerobes adhere strongly to surfaces, as G. Donelli and Co concluded after studying biliary stents biofilms. Furthermore, they discovered that a plurimicrobial biofilm is even more adherent than the monomicrobial one, so the energy of the sound wave used for the dislodgement should be higher. After the dislodgement, the bacteria were grown on specific media brain heart infusion (BHI) broths and then colored with Hucker crystal violet. The colored and then dried plates were examined by using microplate photometers. Even further, field emission scanning electron microscopy (FESEM) or confocal laser scanning microscopy (CLSM) was used [34]. As there are methods described in the literature to evaluate biofilm formation and composition, most of them are expensive and difficult to use. They cannot be used as a bedside method and are not readily available for all intensive care units or hospitals worldwide.

The proposed number of patients to be included in the study is at least 100. This figure might not be achieved if the number of intubated and ventilated patients in our ICU is lower than the number proposed or if other exclusion criteria are met on the way (withdrawn consent, less the 48 h of mechanical ventilation).

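### Aim 2 promises a mean biofilm formation time, but one culture per cannula at removal, with none planned before 48 h, cannot identify that mean without an assumed onset distribution

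*Protocol article*

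**What the plan says.** Section 2.1 (Aims of the Study) gives as its second aim "Detection of the mean period during which the biofilm organizes in the lumen of the cannulae".

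Section 2.5 fixes the cannula data available to answer it. The first specimen comes from "Replacement of the endotracheal cannula at 48–72 h from T_0_ and collection of a cannula specimen". The second comes from "Change of the endotracheal cannula at 168–192 h from T_0_ and the collection of the cannula specimen, sonication, and fluid seeding onto growth media". For each specimen the only readout described is that "The resulting precipitate will be inoculated onto culture media and incubated at 37 degrees to inspect them for bacterial growth". No serial or in-place measurement of a cannula is described.

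The clock starts at T0, defined by "tracheal aspirate collection in the first 2 h after the patient’s admission to the intensive care unit or after tracheal intubation". Section 2.3 excludes "Less than 48 h of mechanical ventilation". Section 3 (Discussions) adds that a patient too unstable for the exchange on schedule leaves the study, so late removals do not add further ages.

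**The concern.** A mean formation time requires knowledge of when biofilm forms across the whole range of times. The design never observes when it forms. It observes, at one moment per cannula, whether bacteria grow. In survival terms these are current-status data: each onset time is either left-censored (positive at removal) or right-censored (negative at removal). The planned removals of first cannulas all fall in one 24-hour window that starts at 48 h from T0.

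Any single mean reported against aim 2 would be read as the time biofilm needs to form. It would in fact reflect either the exchange schedule or an assumption about a period in which nothing was planned to be observed. No choice of analysis removes this, so the conflict is between the stated aim and the stated sampling, not a gap that a statistical analysis plan could fill.

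**Working it through.** The article gives no figure for formation time and no estimator for aim 2, so there is nothing to reproduce. The check is what the sampling in section 2.5 can and cannot determine.

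**Inputs from the protocol article.** First cannula removed 48–72 h after T0; replacement removed 168–192 h after T0; one culture per cannula.

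**Assumptions made here.** T0 is the time of insertion; removal is uniform over 48–72 h (midpoint 60 h); culture detects every colonised cannula. The positive shares below (80%, 95%) are illustrative.

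**Step 1: cannula ages.** First cannula: 48–72 h. Replacement, inserted at 48–72 h: from 168 − 72 = 96 h to 192 − 48 = 144 h.

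**Step 2: bounds on the true mean from first cannulas, with no assumed shape.** Simplify to one inspection at 60 h with positive share p. Each positive has an onset between 0 and 60 h; each negative has an onset after 60 h.
- Lower bound = 0 × p + 60 × (1 − p). Upper bound = 60 × p plus an unlimited contribution from the negatives.
- p = 100%: the mean lies between 0 and 60 h.
- p = 80%: lower bound 60 × 0.20 = 12 h; no upper bound.

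**Step 3: a simple average of removal ages.** Let onset be exponential with mean m. Then
- positive share P = 1 − (m/24)(e^(−48/m) − e^(−72/m));
- mean removal age of positives = {60 − (m/24)[(48 + m)e^(−48/m) − (72 + m)e^(−72/m)]} / P.

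| True mean onset m | Positive share P | Mean removal age of positives |
|---|---|---|
| 12 h | 99% | 60.0 h |
| 24 h | 91% | 60.2 h |
| 48 h | 71% | 60.4 h |
| 72 h | 56% | 60.5 h |

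Simulation with 400,000 onset times agrees. A lognormal onset (log-SD 0.4) with true mean 72 h gives 61.9 h. Holding the true exponential mean at 24 h and moving only a hypothetical removal window from 24–48 h to 48–72 h to 96–120 h moves this average from 36.6 h to 60.2 h to 108.0 h. The average follows the schedule.

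**Step 4: a parametric estimate.** Suppose 80% are positive at 60 h.
- Exponential: mean = −60/ln(0.20) = 37.3 h.
- Lognormal, log-SD 0.4: μ = ln(60) − 0.4 × 0.8416 = 3.758; mean = exp(3.758 + 0.4²/2) = 46.4 h.

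The same data give means about 9 h apart, and the difference comes only from the assumed shape.

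**Step 5: whether the replacement cannula helps.** It enters an airway already exposed to the first cannula, so it describes recolonisation. Even if it were treated as interchangeable with a first cannula, 80% positive at 60 h and 95% at 120 h would give a lower bound of 0.15 × 60 + 0.05 × 120 = 15 h and still no upper bound.

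**The case against.** The strongest reply is that the article names no estimator for aim 2, and that the method may be set out in a statistical plan that is not shown. This stands as far as it goes. A reader might infer that any mean the study reports must come out near 60 h. The documents do not support that: it holds only for a simple average of removal ages. The positive share does carry information (99% falling to 56% in the table above), and a parametric current-status model could return a different value. With 80 of 100 positive, the Wilson 95% interval of 71–87% corresponds under an exponential shape to −60/ln(0.29) = 48.5 h down to −60/ln(0.13) = 29.4 h. That interval covers sampling error only and takes the shape as known.

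A reader might also infer that no cannula younger than 48 h is ever seen. On the cannula's own clock this is not exact. Section 2.5 allows for reintubation within 24 h of extubation, so a cannula at the second exchange could be younger. Patients who arrive already ventilated can have a first cannula older than 72 h. These cases are incidental and do not form a planned early time point.

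A reader might further infer that the replacement-time aim will be calculated from this mean. The article does not say so; the two are listed as separate aims.

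Finally, section 2.1 refers to bacterial load, so the laboratory may record a count as well as growth. That would still be one value per cannula, at removal.

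**Conclusion.** The point holds in this form: aim 2 asks for a mean onset time that the sampling in section 2.5 cannot identify without an assumed onset distribution. The uncertainty is wide: 0 to 60 h if every first cannula is positive, and at least 12 h with no upper limit if 80% are. These bounds rest on a single inspection at 60 h, T0 equal to insertion, perfect culture detection and, for the second, an assumed positive share. Relaxing the first three would change the figures but not restore identifiability. Section 1 itself accepts that some organisms cannot readily be cultured or die before inoculation, which makes a negative result less informative still.

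Severity is moderate. Aim 2 is one of several unranked aims in an observational study. Detection of the bacteria and their comparison with tracheal secretions do not depend on it.

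**What to change.** Replace aim 2 with: the proportion of first cannulas with culturable bacteria at removal, by actual cannula age, with 95% CI, over the ages observed only. Report no mean formation time. State that onset before 48 h is not observed by design. Report replacement cannulas separately, conditional on the first cannula's result. For precision, 80 positive of 100 gives a Wilson 95% CI of 71–87%.

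No new specimens and no change to care are needed. There are two costs. The study gives up a headline formation time. It must also record the cannula insertion time for patients who arrive already intubated, because the data list in section 2.4 does not include it and T0 may be ICU admission for them.

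### Agreement between biofilm and secretion organisms is offered as the ground for early targeted antibiotics, but it cannot show that a positive cannula predicts VAP, and no stated figure does

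*Protocol article*

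**What the plan says.** The fourth aim in section 2.1 compares organisms from the patient's "respiratory secretions with the bacterial load in the biofilm to initiate an early targeted antibiotherapy". The Abstract names the same comparison: "a comparison will be made between the germs in the biofilm and the ones in the tracheal secretion of the patient". It then gives a predictive aim: "The primary purpose is to determine the bacteria before the appearance of a manifest infection".

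The second sentence of the fourth aim adds that "it should be determined whether a clean cannula with a sterile biofilm can prevent the onset of VAP". No measure is attached to either sentence. The Introduction wants sonication to "develop a cheap, sensitive, and specific method for microorganism detection from medical biofilms", which concerns finding organisms in biofilm and not forecasting pneumonia.

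Section 2.4 lists an unspecified outcome item and 28-day mortality, but not the onset of VAP. VAP criteria appear in the Introduction as background. Section 2.3 enrols Group 1, whose respiratory failure is already due to confirmed or strongly suspected pulmonary infection, together with Group 2, whose cause is non-infectious or extrapulmonary. The fourth aim does not separate them.

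**The concern.** The comparator is a second sample from the same airway, while the intended use concerns a later event. A colonised patient who never develops VAP and one who does are both concordant pairs if cannula and aspirate grow the same organism. The agreement figure treats them alike.

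The Introduction says "VAP occurs in 9–40% of intubated patients, representing the most frequent ICU-acquired infection", so on its figures 60–91% of intubated patients do not develop VAP. Any of them with a positive cannula is a positive result without the disease. At stake is the conclusion: good agreement could be reported as support for early antibiotics while the share of positive cannulas followed by VAP remains unknown. The Introduction itself notes that "Prolonged antibiotic therapy and mechanical ventilation increase the risk of serial colonization and reinfection with pathogens", although that remark is about prolonged therapy.

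**Working it through.** **The plan's own figure.** The only size given is in section 3: "The proposed number of patients to be included in the study is at least 100". It comes with no precision target or effect size, so there is nothing to reproduce. I use 100 only as a convenient denominator.

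**Inputs**
- VAP rate v: 9% to 40% (Introduction).
- Sensitivity of cannula culture for VAP: 100%, assumed as the best case.
- Cannula positivity: not given. It is assumed in two ways: p = 50–95% of all cannulas positive, or c = 50–100% of non-VAP patients positive.

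**Step 1: what agreement depends on.** Agreement = pairs with the same result ÷ pairs compared. VAP status is not in the formula. If 90 of 100 pairs agree, agreement is 90% (Wilson 95% interval 83–94%), whether 9 or 40 of those patients later develop VAP.

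**Step 2: PPV from overall positivity.** Per 100 patients, true positives = 100v, positives = 100p, and PPV = v/p.

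| p | v = 9% | v = 40% |
|---|---|---|
| 50% | 9/50 = 18% | 40/50 = 80% |
| 80% | 9/80 = 11% (95% CI 6–20%) | 40/80 = 50% (95% CI 39–61%) |
| 95% | 9/95 = 9.5% | 40/95 = 42% |

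At p = 80%, specificity is 1 − 71/91 = 22% for v = 9% and 1 − 40/60 = 33% for v = 40%.

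**Step 3: PPV from positivity in non-VAP patients.** PPV = v/(v + (1 − v)c).

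| c | v = 9% | v = 40% |
|---|---|---|
| 50% | 0.09/0.545 = 17% | 0.40/0.70 = 57% |
| 80% | 0.09/0.818 = 11% | 0.40/0.88 = 45% |
| 100% | 0.09/1.00 = 9% | 0.40/1.00 = 40% |

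The two forms are consistent: p = 50% with v = 40% leaves 10 positives among 60 non-VAP patients, so c = 17%, which lies below the assumed range for c. That is why Step 2 reaches 80% and Step 3 stops at 57%.

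**Step 4: reading the range.** At v = 9%, positives without VAP are 41/50 = 82% to 86/95 = 91% of all positives over the assumed p. At v = 40% they exceed half only when p is above 80%. With sensitivity of 90% instead, the Step 2 extremes move to 8.1/95 = 8.5% and 36/50 = 72%.

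The agreement in Step 1 is compatible with every entry in both tables.

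**The case against.** Several points on the other side have force.

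- **The prevention sentence.** Asking whether a sterile biofilm prevents VAP needs VAP status by biofilm status, and that table contains the colonised-without-VAP cell. A reader might infer that the plan ignores such patients altogether; the article does not support that. What remains is that the sentence asks about clean cannulas and does not make the antibiotic inference depend on how many positives progress.
- **The word "targeted".** The aim can be read as choosing which organism to cover, for which concordance is relevant. That stands. The Abstract's wish to act before overt infection still leaves a predictive use that concordance cannot serve.
- **No success rule.** A reader might infer that a test giving mostly false alarms would be declared a success. The article names only a comparison, with no threshold, so this cannot be said.
- **High agreement is not documented.** Section 3 says sonication may detect more than traditional culture and may also cost viability, so discordance is possible. The point needs only that agreement, if high, is uninformative about VAP.
- **Unseen documents.** The choice of accuracy measures can properly sit in a full protocol or SAP, and VAP onset might fall under the unspecified outcome item. Their absence alone would be no finding. The point rests on the inference that the aim itself states.
- **Patient care.** Section 2 says the study leaves treatment to the attending physician, so the risk lies in the conclusion and not in the management of enrolled patients.

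**Conclusion.** The point holds in this form: the comparison that the article names cannot support the predictive part of the use it gives for it. Concordance may inform organism choice. Whether a positive cannula precedes VAP needs later VAP as the comparator, and no stated figure supplies that.

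The possible PPV runs from about 9% to 80%. This rests on the Introduction's VAP range, perfect sensitivity and assumed positivity, none of them measured in this population. The 9–40% refers to intubated patients generally, whereas this study takes those ventilated for more than 48 h and includes Group 1. That positives would be mostly false alarms is therefore possible but not established; at the upper VAP rate it depends wholly on positivity.

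**What to change.** 1. In section 2.4, name VAP onset as a recorded outcome, with its date and the criteria given in the Introduction.
2. Under the fourth aim, in patients without pulmonary infection at T0 (Group 2), report PPV and negative predictive value with 95% confidence intervals for first-cannula growth against VAP arising after that sample. Show the same figures for the 48–72 h aspirate alongside.
3. Report these by antibiotic exposure after sampling. Note that taking the specimen means exchanging the cannula (section 2.5), and that exchange and usual-care antibiotics may both prevent VAP. The observed PPV may therefore be lowered and is not a pure false-alarm rate.
4. State that organism agreement alone will not be used to conclude that a biofilm result supports starting antibiotics.

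The cost is one reworded aim, one added data item, and a 2×2 table per specimen type, split by antibiotic exposure. Intervals will be wide because only Group 2 counts and its size is not given. Even 80 positives gave 39–61% above, and fewer will give more width. The conclusion may also be less favourable than one based on agreement.
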